##### Sick leave

Self-reported percentage of sick leave will be collected pre- and post-treatment as well as 6 and 12 months follow-up. In addition, the study has permission to collect data from national register data on the percentage of sick leave up to 24 months prior to treatment and 48 months after treatment. Norway has extensive national registries for sick leave and benefit pay-outs, creating a unique opportunity to evaluate treatment effects in this regard. The 2 years prior to treatment will serve to establish a baseline. Figure 2 shows the schedule for the collection of self-report measures.

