**Methods:**

The study is a randomised controlled wait-list trial (RCT; *N* = 240). The intervention group will receive protocol-based MCT and work-focused interventions immediately after inclusion. The control condition is a wait-list control group. All patients will receive up to 12 weekly sessions. The study context is a Norwegian outpatient clinic part of a national programme aimed at reducing sick leave. The co-primary outcomes are change in RTW and symptoms of depression and anxiety at the end of treatment. In addition to self-report, sick leave will also be collected from national registries from 2 years prior to intervention to 4 years after intervention. Symptoms of depression and anxiety will be collected by self-report at pre- and post-treatment and at 6 and 12 months follow-up after treatment. A cost-effectiveness analysis will use total cost and quality-adjusted life-years as the secondary outcomes.

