In addition to the need for more rigorous studies, there is also room for improving treatment outcomes [22]. The majority of the work-focused treatment studies have been modelled on CBT as the evidence for its efficacy in treating depression and anxiety symptoms is well explored [11]. The research in general shows significant improvement in symptoms in approximately 50% of patients but this masks considerable variability in outcomes across studies [23, 24]. Furthermore, a treatment where half of the patients do not get significantly better leaves considerable room for improvement. Follow-up of 1- and 2-year relapse rates show that 25–50% of patients treated for depression relapse, and the corresponding number for anxiety is about 15% [25, 26]. In recent years, metacognitive therapy (MCT) has shown excellent results in treating depression and anxiety [27]. Recent studies on MCT in Norway have shown recovery rates of 65% and 70% for anxiety and depression, with similar rates at 1 and 3-year follow-up [28–31]. In Denmark a comparison of MCT with CBT for depression showed that MCT was superior, achieving a 74% recovery rate compared with 52% in CBT [32]. A separate Norwegian study also showed that metacognitions, a central construct in MCT, may also predict work status [33]. This indicates that MCT is a very promising treatment which may represent a significant step forward in terms of recovery from depression and anxiety and may be more effective than existing approaches.

An observational study at Diakonhjemmet Hospital in Norway, which included work-focus interventions found that significantly more patients returned fully to work at end of treatment in the intervention group than in the wait-list group (41.4% versus 26.3%) [34]. The findings from this study are promising, warranting further exploration in a RCT.

To date, no study has investigated Metacognitive therapy (MCT) and work-focused interventions together. This waitlist RCT primarily evaluates the changes in symptoms of depression and anxiety, and percentage of sick leave, and secondarily whether the treatment is cost-effective. The main hypotheses to be tested are:

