MCT plus work-focused interventions will be superior to the wait-list condition in reducing symptoms of anxiety and depression and the percentage of sick leave. Results will examine post-treatment and for the intervention group at 6 and 12 months follow-upMCT plus work-focused interventions will be cost-effective when compared with the wait-list condition. Self-report data on the percentage of sick leave will examine post-treatment, 6 and 12 months follow-up, in addition with the national register data span from 24 months prior to treatment and 48 months after ending the treatment

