### Study design

The study is an RCT comparing MCT and work-focused interventions given immediately after screening (< 1 week after assessment) with a wait-list condition. We chose a waitlist design as a “no treatment” control group is not feasible due to ethical reasons, and comparison with another active treatment was not feasible due to practical reasons. The intervention will be given as manualised treatment based on diagnostic-specific MCT as specified in the manual from 2009 by Wells [44]. Work-focused interventions will be based on the work module used in Lagerveld’s study but adjusted for a Norwegian context and MCT [18].

A summary flowchart of the procedure is found in Fig. 1. Treatment duration is up to weekly 12 sessions, but as the study takes place in a national health service outpatient clinic, the number of sessions may vary. The treatment primary outcome is measured at end of treatment or session 12 if treatment duration is longer, whichever comes first. In all, 240 patients who are on sick leave due to anxiety or depression at the time of enrolment will be recruited. The study uses a block randomisation with a stratification based on gender and degree of sick leave to ensure an equal balance of gender and sick leave across the conditions. Degree of sick leave indicates the percentage of ordinary working hours. Someone working half their normal number of hours would thus be on 50% sick leave. An equal number of patients are randomised to the treatment and wait-list condition. The waitlist condition group is subdivided into two equal groups that wait either 8 or 12 weeks before treatment, because in the sample there will be variation in the duration of the treatment intervention. The registry data will benchmark the current study against previous studies that have used CBT with regards to RTW. The maximum waiting time of 12 weeks is identical to the average waiting time at the clinic, to ensure that participation in the study does not delay treatment for patients. The reason for differentiating the waitlist condition is twofold. First, Norwegian law dictates that patients with moderate to severe depressive episodes should not wait longer than 8 weeks. Secondly, it is important to investigate if the duration of waiting in itself accounts for differences in change, e.g. whether shorter or longer waiting times improves outcomes.

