### Eligibility criteria

Participants must:
Be adults of working age (18–67 years)On sick leave either partial or full, due toAnxiety and/or mild to moderate depressive disorders, assessed using MINI International Neuropsychiatric Interview,Eligible for work-related sick leave payouts, andProvide written consent

In addition to the inclusion criteria, participants will be excluded if they are:
Suffering from psychosis (i.e. bipolar disorder, schizophrenia or other psychotic disorders)Engaged in active substance abuseSuffer from cluster A or B personality disorder

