### Randomisation and blinding

After the initial screening session, eligible patients will be randomised using WebCRF, a web-based program provided by the Unit for Applied Clinical Research at the Norwegian University of Science and Technology (NTNU). The block randomisation is stratified on gender and degree of sick leave. The study will include 240 patients in all. Half of the patients will be allocated to the treatment condition (*n* = 120) and the other half to the wait-list conditions (*n* = 120). Half of the patients in the wait-list condition wait 8 weeks, the other half wait 12 weeks before commencing treatment. Because the treatment is offered in an ordinary outpatient clinic, the duration of the treatment will vary. To control for potential differences in treatment duration the wait-list condition also contained two different conditions.

Guidelines from the Norwegian Directorate for Health and Social Affairs state that patients who fulfil the criteria for a moderate depressive episode according to ICD-10 have the right to specialised health care within 8 weeks of referral [45, 46]. Thus, patients with this diagnosis will be allocated evenly between the treatment condition and the 8-week waiting condition. No patients with moderate depressive episode will be allocated to the 12-week waiting condition due to Norwegian law.

The randomisation procedure is performed by administrative personnel who otherwise are not involved in the patient’s treatment. Clinicians are not involved in the randomisation procedure. The initial assessment session is carried out by a different therapist than the one the patient sees for treatment. Blinding the treatment therapist to group allocation is not doable for logistical reasons (e.g. date of journal documents). Assessment of diagnosis at end of treatment using the Mini-International Diagnostic Interview is carried out by an independent clinician who has no prior contact with the patient.

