### Sample size estimate

Sick leave will be operationalised as a percentage of sick leave collected both from the national registry and self-report. To evaluate the intervention versus wait-list condition, the percentage of sick leave status of the intervention group will be compared at end of treatment to the status of the control group at the end of the waiting period. The minimum expected effect is that of the treatment reported in the naturalistic follow-up study at the same clinic [56]. Data from this study showed a self-reported full RTW response rate of 0.41 in the intervention group versus 0.26 in the wait-list control group, with a pooled standard deviation of 0.4 [34]. Given this result, to detect differences in a dichotomous outcome variable we would need approximately 120 in each treatment group to have an 80% chance of detecting a significant difference at a two-sided significance level of 0.05 [63]. For the anxiety and depressive symptoms, detecting a 5 point difference between intervention and waitlist control group using a pooled standard deviation of 6.95, we need approximately 31 participants in each of the group in order to have an 80% chance of detecting a significant difference at a two-sided significance level of 0.05 [28, 64].

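### Beyond the waiting period there is no untreated comparator, so the 6-month, 12-month and before-after registry results cannot carry a treatment-effect claim

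*Protocol article*

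**What the plan says.** Under Study design, "240 patients who are on sick leave due to anxiety or depression at the time of enrolment will be recruited", and the eligibility criteria read "On sick leave either partial or full". The control condition is short. Randomisation and blinding states: "Half of the patients in the wait-list condition wait 8 weeks, the other half wait 12 weeks before commencing treatment". After that everyone is treated; the abstract says "All patients will receive up to 12 weekly sessions".

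The controlled sick-leave contrast is given under Sample size estimate: "the percentage of sick leave status of the intervention group will be compared at end of treatment to the status of the control group", whose status is taken when its wait ends. Primary objectives likewise sets the main question at end of treatment and assigns other time points to the secondary objectives.

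For the later period, the first main hypothesis in Background claims superiority to wait-list and continues "Results will examine post-treatment and for the intervention group at 6 and 12 months" of follow-up. Primary objectives lists change in registry sick leave from 2 years before to 4 years after the intervention. The Sick leave section names the 2 years before treatment as the baseline and describes the registries as "creating a unique opportunity to evaluate treatment effects in this regard". The only other long-term reference, under Study design, is a benchmark against earlier CBT studies, which is external and consists of treated patients.

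**The concern.** A change from baseline within treated patients estimates a treatment effect only if those patients would otherwise have stayed where they were. That is implausible for people enrolled because they are on sick leave, since some return to work without therapy. The wait-list measures this natural return, but only for 8 or 12 weeks. The follow-up and registry results extend far past that point, and the article words them in terms of superiority and treatment effects.

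The limitations in the Discussion cover the short wait, the 8-week regulation and the single centre. They do not mention spontaneous return to work or regression to the mean. If the wording stands, natural recovery could be reported as durable benefit, in a trial whose Discussion hopes to inform policy.

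**Working it through.** The article states no figure for the long-term effect, so there is none to reproduce. The check sets the before-after reading against the controlled reading using the article's own return rates, then asks how far natural return might go by the follow-up visits.

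**Inputs from the article**
- Full return to work in the clinic's earlier observational study: 41.4% treated, 26.3% wait-list (Background; rounded to 0.41 and 0.26 under Sample size estimate).
- Full return at entry: 0%, because every participant is on partial or full sick leave. The intervention arm starts within a week of assessment, so this is also its pre-treatment level. The same starting point is taken for the earlier study.
- Follow-up at 6 and 12 months after treatment of up to 12 weekly sessions. Taking 12 weeks of treatment, these fall at weeks 12 + 26 = 38 and 12 + 52 = 64.

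**Step 1. Before-after versus controlled, at end of treatment**
- Before-after in the treated group: 41.4 − 0 = 41.4 points.
- Controlled difference: 41.4 − 26.3 = 15.1 points.
- Share of the before-after change also seen without treatment: 26.3 / 41.4 = 0.635, about 64% (0.26 / 0.41 = 0.634 with the rounded rates).

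**Step 2. Natural return at the follow-up visits (illustration only)**

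Assume that the 26.3% was reached by 12 weeks. The weekly rate is h = −ln(1 − 0.263) / 12 = 0.0254. After week 12, let the rate be multiplied by f. Natural full return at week t is 1 − exp{−h[12 + f(t − 12)]}.

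| Rate after week 12 | Week 38 | Week 64 |
|---|---|---|
| Constant (f = 1) | 62% | 80% |
| Halved (f = 1/2) | 47% | 62% |
| Quartered (f = 1/4) | 38% | 47% |

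For example, with f = 1/4 at week 38 the exponent is 0.0254 × (12 + 6.5) = 0.470, and 1 − exp(−0.470) = 0.375. If the 26.3% had been reached by 8 weeks, the constant-rate figures would be 77% and 91%. The calculation ignores relapse onto sick leave. A return rate that falls with time is more plausible than a constant one, so the first row is an upper-end case.

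**Step 3. The registry**

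This arithmetic does not carry over directly to the registry outcome. Against the level at entry, natural return would flatter the change. Against a 2-year average that includes months before the current sick-leave episode, later sick leave could look better, unchanged or worse. The Sick leave section does not say which reference applies. Recruitment process and context adds that sick-leave compensation runs for up to one year and is then replaced by another benefit. Recorded sick leave could therefore also fall without any return to work, depending on which benefits are counted.

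**The case against.** The strongest reply is that the article never writes down a before-after estimate. A baseline may equally be a covariate or a first time point in a between-arm model. The data analysis section promises intention-to-treat analysis of all randomised patients with linear mixed models under a plan that is not shown. The primary objective is tied to end of treatment, and the phrase about the intervention group can be read as plain follow-up of that arm. Losing the untreated arm is the usual price of a wait-list design, which the article justifies on ethical and practical grounds.

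Much of this stands. A reader might infer that no by-arm long-term analysis is planned; without the analysis plan, that cannot be said. A reader might also infer that sick leave can only stay level or fall after entry. That is wrong here: partial leave is eligible, so a patient on 50% can move to 100%, and a patient who has returned can relapse. Only binary full return has a floor at zero, whereas the planned outcome is the percentage of sick leave.

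The reply does not rescue the long-term wording. The 6- and 12-month results sit within a superiority hypothesis and are confined to one arm, and the registry data are offered for evaluating treatment effects. Even a by-arm model, once both arms are treated, would compare earlier with later treatment rather than treatment with none.

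**Conclusion.** The concern holds for the 6-month, 12-month and before-after registry results, and only for those. The end-of-treatment comparison keeps its randomised control.

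On the earlier study's figures, about 64% of a before-after gain in full return would also appear without treatment by the end of the wait. That study was observational, so its 15.1-point difference is controlled but not randomised. The natural-return ranges of 38% to 62% at 6 months and 47% to 80% at 12 months rest on an assumed 12-week wait and assumed later rates. They show that high full-return figures in the treated arm could arise with no treatment effect; they do not predict what the trial will find.

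A reader might go further and conclude that every long-term analysis would show a large benefit from an inert treatment. The documents do not support that for the registry, where the size and direction of bias depend on an unstated reference, or for percentage sick leave, which can rise. This is a point that should be corrected; it does not undermine the main comparison.

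**What to change.** In the main hypotheses (Background) and the Sick leave section:

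1. Limit the superiority or treatment-effect claim to the randomised comparison at end of treatment versus end of wait.
2. Present the 6-month, 12-month and before-after registry results as the descriptive course of treated patients. State whether the registry reference is the level at entry or the 2-year average.
3. State one intention-to-treat comparison, by randomised arm, of cumulative registry sick leave counted from the randomisation date, for example over 12 and 48 months. Label it immediate versus 8-to-12-week-delayed start, not treatment versus no treatment.

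The cost is a change of wording and one extra analysis on registry data already permitted. The long-term claim becomes more modest, and the by-arm contrast reflects only the effect of starting 8 to 12 weeks earlier.

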**Fig. 2 Fig2:**
[figure not shown]
SPIRIT figure. Schedule of enrolment, interventions, and assessment*. Abbreviations: BAI* Beck’s Anxiety Inventory; *BDI-II* Beck’s Depression Inventory-II; *EQ-5D* Euro-Qol 5D; *RTW-SE* Return to Work Self-efficacy; *MCQ-30* Metacognitive Questionnaire 30; *SHC* Subjective Health Complaints; *RSA* Resilience Scale for Adults; *RTW-E* Return to Work Expectation; *SNAQ* Short Negative Acts Questionnaire; *NAQ-R* Negative Acts Questionnaire Revised; *AUDIT* Alcohol Use Disorders Identification Test; *SAPAS-SR* Standardised Assessment of Personality Self-report; *M.I.N.I* Mini-International Neuropsychiatric Interview

#### Secondary outcome measures

##### EuroQol five-dimensional descriptive system

The EQ-5D 5L is generic a self-report measure for describing and valuing health status. Health is described in five dimensions (5D): Mobility, Self-Care, Usual Activities, Pain/Discomfort and Anxiety/Depression. Each dimension has five levels (5L) scoring from no to extreme problems. The EQ-5D-5L also includes a rating of own health on a 0–100 visual analogue scale. Quality-adjusted life years (QALY) will be estimated from the EQ-5D-5L using the English utility tariff, which will support the cost-effectiveness analysis [37]. The use of the EQ-5D-5L for evaluating health technology in Norway is recommended by the Norwegian Medicines Agency [48].

##### Return to Work Self-Efficacy Scale

RTW-SE is an 11 item self-report questionnaire of self-efficacy in returning to work. Respondents are asked how they would deal with overcoming obstacles and respond to statements such as “I will be able to cope with potential problems at work” or “I will be able to manage set-back” using a six-point Likert scale. Both baseline score and change in the score during treatment have been shown to be robust predictors of return to work [49]. The scale has also been validated in a Norwegian sample [50].

##### Metacognitions Questionnaire 30

MCQ-30 measures metacognitive beliefs in a 30-item self-report questionnaire. Beliefs are scored across five factors: cognitive confidence, positive beliefs about worry, cognitive self-consciousness, negative beliefs about the uncontrollability of thoughts and danger and beliefs about the need to control thoughts. Higher scores indicate higher levels of maladaptive metacognition. The validity and reliability of MCQ-30 is well-established in adults [38], including in Norwegian samples with depression and anxiety [51].

##### Subjective Health Complaints

SHC is a self-report questionnaire measuring subjective health complaints along five factors: musculoskeletal pain, pseudo-neurology, gastrointestinal problems, allergy and flu. The aim of the SHC is to provide a simple measure of the most common complaints seen by general practitioners, and it was developed and validated using Norwegian patient samples [42].

##### The Resilience Scale for Adults

RSA is a self-report questionnaire measuring self-efficacy across five subscales: personal competence, social competence, family coherence, social support and personal structure. Respondents answer 33 items using a seven-point Likert scale. The RSA scale is a valid and reliable measurement of protective factors important to regain and maintain mental health. Three of the RSA subscales have previously been shown to be a significant predictor of employment status in a Norwegian sample [41].

##### Return to Work Expectation

RTW-expectation is a single-item scale measured by participant response to the following statement “I expect to return to work within the next few weeks” on a five-point Likert scale. RTW-expectation has been used in several previous studies and has been shown to predict future benefit recipiency in a Norwegian sample of patients with depression and anxiety struggling with work participation [52].

##### The Negative Acts Questionnaire-revised

NAQ-R is a 22 item self-report questionnaire developed to measure exposure to bullying in the workplace. It has a Cronbach’s alpha for the 22 items of .90, indicating excellent internal consistency, and has been shown to be valid in a Norwegian sample [39].

##### Alcohol Use Disorder Identification Test

AUDIT is a questionnaire used to screen for alcohol abuse. It has ten questions and yields a score range of 0–40 with higher scores indicating more severe problems [53]. It has been shown to have good psychometric properties including high test-retest reliability across multiple studies [54].

##### The Standardised Assessment of Personality Abbreviated Scale – Self report

SAPAS-SR is an 8 item self-report questionnaire. It has shown good sensitivity (80%) and specificity (83%) in identifying personality disorders in clinical populations [55].

